#### Per-operative

Prior to placement of the stent, a DSA in two imaging planes, with at least 30, but preferably more than 45 degrees difference in rotation will be performed, and a systolic pressure gradient will be measured. After successful stent placement, a DSA (in two imaging planes) and systolic pressure gradient will once again be performed. If open surgical and/or endovascular repair of other arteries of the lower extremity was performed, this will be documented. Any complication that occurred during the procedure will be documented.

#### 1 month postoperative

At 1 month, patients will undergo an ABI with treadmill test (patients with persistent CLI will only require ABI measurement in rest). Any complication that occurred within the first 30 days will be scored. Patients will be asked to fill in the RAND-36 and the WIQ.

#### 6, 12 and 24 months postoperative

At 6, 12 and 24 months, ABI and treadmill test will be performed, as well as a DUS, and patients will be asked to fill in the RAND-36 and WIQ. If DUS shows a stenosis, defined as a peak systolic velocity rate of ≥2.4, or is inconclusive, CT-A, MR-A or DSA will be performed. If an in-stent stenosis or occlusion is identified, this will be documented and treated within 1 month. Table 3 summarizes the study procedures at different moments.

**Table 3 T3:** Study procedures

	**Pre-ope-rative**	**Per-ope-rative**	**1 month**	**6 months**	**12 months**	**24 months**	**In case of restenosis**
DUS	X			X	X	X	X
ABI (with or with-out treadmill test)	X		X	X	X	X	X
DSA		X					X
WIQ/RAND-36	X		X	X	X	X	

DUS = Duplex ultrasonography, ABI = Ankle-brachial index, DSA = Digital subtraction angiography, WIQ = Walking Impairment Questionnaire, RAND-36 = RAND 36-Item Health Survey.

#### Unplanned visits

Patients might present themselves at the outpatient clinic or the emergency ward in between study visits, with (recurrent) symptoms and complaints of PAOD. In this case at least ABI in rest and DUS is mandatory. If DUS shows a stenosis, defined as a peak systolic velocity rate of ≥2.4, or is inconclusive, CT-A, MR-A or DSA will be performed. If an in-stent stenosis or occlusion is identified, this will be documented and treated within 1 month. Patients will then resume their regular follow-up scheme as planned.

### Withdrawal of individual subjects

Subjects can leave the study at any time for any reason if they wish to do so without any consequences. The investigator can decide to withdraw a subject from the study for urgent medical reasons. This will be recorded in the CRF and the physician is required to notify the Principal Investigator.

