### Replacement of individual subjects after withdrawal

Patients that have been randomized and are withdrawn from the study will be not replaced. They will be considered lost to follow-up and included in the data analysis based on intention-to-treat. Patients that have been included but are withdrawn prior to randomization will be replaced. This will be documented.

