### Follow-up of subjects withdrawn from treatment

Patients that for whatever reason receive a different treatment than randomized, or received no treatment will be followed-up and included in the trial, based on intention-to-treat. Patients that are withdrawn from follow-up will be considered lost to follow-up.

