#### Follow-up of adverse events

All adverse events will be followed-up until they have abated, or until a stable situation has been reached. Depending on the event, follow up may require additional tests or medical procedures as indicated, and/or referral to a general physician or a medical specialist

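### Investigator withdrawal for urgent medical reasons ends all study observation of a randomized patient with a permanent stent, where only study visits or procedures need stop

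*Protocol article*

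**What the plan says.** Three consecutive sections of the protocol article set the rule.

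- **Withdrawal of individual subjects** gives the power in one sentence, which reads "The investigator can decide to withdraw a subject from the study for urgent medical reasons". What counts as urgent is not defined further. The only process attached is a case report form entry and notice to the lead investigator.
- **Replacement of individual subjects after withdrawal** says that nobody takes the place of a patient who leaves after randomization. On the status of those who leave, it reads "They will be considered lost to follow-up and included in the data analysis based on intention-to-treat".
- **Follow-up of subjects withdrawn from treatment** keeps under observation anyone who was given the other stent or no stent. It handles those taken out of observation otherwise, in these words: "Patients that are withdrawn from follow-up will be considered lost to follow-up".

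Two other sections bear on the point. The one on adverse events is general in scope and makes no exception for withdrawn patients: "All adverse events will be followed-up until they have abated, or until a stable situation has been reached". The one on unplanned visits requires ABI and duplex for recurrent symptoms, and a stenosis or occlusion found in the stent has to be recorded and dealt with. After that, the patient stays in the trial: "Patients will then resume their regular follow-up scheme as planned".

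**The concern.** The randomized treatment is a single permanent implant. Once it is in place there is no randomized treatment left to stop, so taking a patient out of the study chiefly means no longer looking. The protocol knows the difference between departing from treatment and leaving follow-up, because it keeps patients with the wrong stent or no stent under observation. It does not draw that line for a patient withdrawn on medical grounds.

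Two kinds of analysis are exposed. Restenosis and reocclusion are analysed by life table and log-rank test (Actuarial analysis). There a patient lost to follow-up is censored, and the method assumes that censoring is unrelated to prognosis, which is doubtful when the reason is medical. Target-lesion revascularization, mortality, amputation and complications are compared by chi-squared test (Univariate analysis). That test has no censoring, so a patient with unknown outcome must be dropped or counted as event-free. The protocol also expects negligible mortality and plans restenosis-free survival analyses to check this. The check is weaker if deaths after withdrawal are not gathered.

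**Working it through.** **Step 1: what happens to each kind of patient under the stated rules.**

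| Situation after randomization | Still observed? | Section |
|---|---|---|
| Different treatment or none | Yes | Follow-up of subjects withdrawn from treatment |
| In-stent stenosis or occlusion found at an unplanned visit | Yes, regular scheme resumes | Unplanned visits |
| Adverse event | That event, until abated or stable | Follow-up of adverse events |
| Withdrawn by the investigator for an urgent medical reason | No; lost to follow-up, earlier data kept | Withdrawal and Replacement sections |

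Only the last row ends observation by someone other than the patient. No section provides for later imaging, re-intervention, amputation, vital status or new serious events in that patient.

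**Step 2: reproduce the planning figure.** Inputs from Sample size calculation: 90% v 72% free of restenosis at 2 years, alpha 0.05 (taken as two-sided), power 0.80.

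- Hazard ratio = ln(0.90)/ln(0.72) = 0.321.
- Freedman events = (1.960 + 0.842)² × (1.321/0.679)² = 29.7.
- Per group = 29.7/(0.10 + 0.28) = 78.1, rounded up to 79. This matches the protocol.
- Loss allowance: 79 × 1.10 = 86.9, so 87 per group, as stated. Loss below 10% of 87 means at most 8 patients per arm.

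**Step 3: expected failures.** Covered: 87 × 0.10 = 8.7, about 9. Control: 87 × 0.28 = 24.4, about 24. In total 87 × 0.38 = 33.1 events, giving Freedman power of 84%.

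**Step 4: illustrations.** The protocol gives neither the number nor the outcome of medical withdrawals, so the counts below are assumptions. Each range runs from censoring at the start to censoring at the end of follow-up.

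- *5 of 24 control failures unseen:* 19/82 = 23.2% to 19/87 = 21.8% failing, so 76.8% to 78.2% restenosis-free instead of 72%. Against 90%, the 18-point difference becomes about 12-13 points.
- *4 of 9 covered failures unseen:* 5/83 = 6.0% to 5/87 = 5.7% failing, so about 94% instead of 90%. Against 72%, the difference becomes about 22 points.
- *Power, with the hazard ratio held at 0.321:* 82% with 2 events unseen, 79% with 4, 76% with 6 and 73% with 8.

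**Step 5: extreme bounds.** Suppose 8 per arm are withdrawn at the start and the 79 retained show 90% v 72%. Retained failures are 79 × 0.10 = 7.9 and 79 × 0.28 = 22.1.

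| Unseen failures among the 8 withdrawn | Covered | Control | Difference |
|---|---|---|---|
| All, both arms | 1 − 15.9/87 = 82% | 1 − 30.1/87 = 65% | 16 points |
| Covered arm only | 82% | 1 − 22.1/87 = 75% | 7 points |
| Control arm only | 1 − 7.9/87 = 91% | 65% | 26 points |

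The bounds lie on both sides of 18 points, so no direction of bias can be claimed.

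**The case against.** A reader might infer that the sickest patients vanish from both the safety and the primary-endpoint data. The documents do not support that. Withdrawn patients stay in the intention-to-treat analysis, so a restenosis seen before withdrawal counts as an event and time at risk up to withdrawal counts too. All adverse events are recorded, related or not, and the one that prompted withdrawal should be followed until abated or stable. That section is not reconciled with the withdrawal sections, but it does not contradict them. That the patients concerned are the sickest is an inference from the word urgent.

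Nor does restenosis or occlusion itself lead to withdrawal: Unplanned visits has it documented and the patient returned to the schedule. This makes the assumed counts in Step 4 look high. They would also use about half of an allowance that must cover every other cause of loss.

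A reader might also infer that the person withdrawing the patient knows the stent. The protocol says that the operating physician is unblinded and that the code may be broken for re-intervention. It does not say that either applies to the investigator who withdraws a patient.

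The clause has legitimate uses. Consent precedes angiography and randomization, so it also serves the pre-randomization stage. After the procedure, participation still brings extra visits, duplex scans and treadmill tests (Benefits and risks assessment), and a medical reason to stop those is sensible.

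Finally, a condensed article may leave chart-based data collection to the full protocol. That would answer a complaint about missing detail. Here the article states a rule, and followed as written it ends observation. An analysis plan cannot recover data that were never collected. These objections narrow the point but leave that part standing.

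**Conclusion.** The point holds in limited form. For a randomized patient, investigator withdrawal on medical grounds is withdrawal from the whole study and leads to lost-to-follow-up status. Outcomes after that moment are not provided for, although the implant remains. Censoring may then be informative in the primary and reocclusion analyses, and the chi-squared endpoints are left with unknown outcomes.

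The size is not known. About 33 restenosis events are expected in all, so a handful unseen would matter: about 5 percentage points on the control rate in the first illustration, and power down from 84% to 76% with 6 events unseen. These figures rest on assumed counts and on every such withdrawal concealing a failure. They show scale only and are not an estimate of bias. The change is worth making because it is cheap and cannot be made good after the data are lost.

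**What to change.** Revise the three sections together so that stopping study visits or procedures is distinct from ending observation.

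- **Withdrawal of individual subjects:** for randomized patients, let the investigator's medical decision stop study visits or procedures only. Data collection ends only when the patient withdraws consent.
- **Replacement and Follow-up sections:** state that a patient whose study procedures stop for medical reasons is not classed as lost to follow-up. Vital status, amputation, re-intervention, serious adverse events and any iliac imaging obtained in routine care are taken from hospital records up to 24 months.
- Add a cross-reference to Follow-up of adverse events so that it plainly applies to these patients.

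This alters what is recorded and leaves clinical care to the treating team. The cost is protocol wording and chart review for probably few patients. The drawback is that some outcomes will come from routine records, with less regular timing and without the blinded study assessment.

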### Replacement of individual subjects after withdrawal

Patients that have been randomized and are withdrawn from the study will be not replaced. They will be considered lost to follow-up and included in the data analysis based on intention-to-treat. Patients that have been included but are withdrawn prior to randomization will be replaced. This will be documented.

### Follow-up of subjects withdrawn from treatment

Patients that for whatever reason receive a different treatment than randomized, or received no treatment will be followed-up and included in the trial, based on intention-to-treat. Patients that are withdrawn from follow-up will be considered lost to follow-up.

### Premature termination of the study

If at any point during the study information becomes available, either from interim analysis of results, or from external sources, that the investigated device poses an increased risk for participating patients, the study will be terminated. Patients will be unblinded for the type of stent they received. If applicable, they will receive additional treatment or intervention.

### Safety reporting

#### Section 10 WMO event

In accordance to section 10, subsection 1, of the WMO, the investigator will inform the subjects and the reviewing accredited medical ethical review committee (METC) if anything occurs on the basis of which it appears that the disadvantages of participation may be significantly greater than was foreseen in the research proposal. The study will be suspended pending further review by the accredited METC, except insofar as suspension would jeopardize the subjects’ health. The investigator will take care that all subjects are kept informed.

#### Adverse and serious adverse events

Adverse events are defined as any undesirable experience occurring to a subject during the clinical trial, whether or not considered related to the investigational treatment. All adverse events reported spontaneously by the subject or observed by the investigator or his staff will be recorded.

A serious adverse event is any untoward medical occurrence or effect that:

• Causes death, or is life threatening (at the time of the event);

• Requires hospitalization or prolongation of existing inpatients’ hospitalization;

• Results in persistent or significant disability or incapacity.

All SAEs will be reported by the responsible investigator through the web portal ToetsingOnline to the accredited METC that approved the protocol within 15 days after the sponsor has first knowledge of the serious adverse reactions.

SAEs that result in death or are life threatening should be reported expeditiously. The expedited reporting will occur not later than 7 days after the responsible investigator has first knowledge of the adverse reaction. This is for a preliminary report, with another 8 days for completion of the report.

#### Follow-up of adverse events

All adverse events will be followed-up until they have abated, or until a stable situation has been reached. Depending on the event, follow up may require additional tests or medical procedures as indicated, and/or referral to a general physician or a medical specialist

#### Data safety monitoring board

Following the recommendations of the ’Quality assurance in human medical research’ charter (Dutch: Kwaliteitsboring van mensgebonden onderzoek) by the ‘Dutch Federation of Academic Medical Centers’ (Dutch: Nederlandse Federatie van Universitair Medische Centra), we do not consider the formation of a Data Safety Monitoring Board (DSMB) sensible. A DSMB has several functions. First, is to assess whether statistical significance can still likely be reached or, on the other hand, may be reached preliminarily for the main outcomes, and thus whether the study group size should be changed. However, our main outcomes are all scored at 2 years. So, when a relevant group has reached the 2-year follow-up, and an interim analysis would be sensible, we will already have included all of our patients. So, the interim analysis would not contribute anything on that field.

A second function of the DSMB is to assess the safety and (S)AE’s of the investigational products. However, all stents that are used in the trial are registered for use in the iliac artery and have been used for years. As well, virtually all complications are procedure-related and not stent-related. Therefore, a difference in safety or occurrence of (S)AE’s is unlikely. Of course, the investigators and the METC will monitor the occurrence and rate of (S)AE’s.

### Statistical analysis

Statistical analysis will be performed for the complete study population, as well as subgroup analysis for patients with IC vs CLI, occlusions vs stenoses, and endovascular vs hybrid procedures.

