Mwipatayi, 2011	Randomized controlled trial	83 covered	Both	18 month: 92%	18 month: 75%
		84 uncovered			

As shown in Table 2, primary patency rates of covered stents are excellent. However, most studies are either retrospective or do not have a control group. Only one randomized controlled trial has been performed, which is the COBEST-trial (Covered versus Balloon Expandable Stent Trial). This trial compares the Advanta V12 balloon-expandable PTFE-covered stent versus uncovered stents. In this trial, various types of uncovered stents are used, including self-expanding. Since balloon-expandable and self-expanding stents have very different characteristics, this is likely to influence the results. Some of the other drawbacks of this study include usage of the TASC-classification for sub-group analysis, and making no distinction between the CIA and the EIA. The TASC-classification is a very general and heterogenous classification, making it useful for day to day practice, but not so much for research purposes. Categorizing subgroups based on specific lesion characteristics (such as occlusion vs stenosis, and length of the lesion), allows for much more accurate analysis. Furthermore, the external and common iliac have very different anatomical characteristics. Where the CIA is a straight and immobile vessel, being fixed to the sacral promontory, the EIA has a much more tortuous course, along with stretching during extension of the hip [51]. To our knowledge, no comparative studies have been published on this topic, but biomechanical studies do confirm our opinion [42]. Furthermore, a retrospective study showed a decreased patency rate after stent placement in the EIA compared to a similar treatment in the CIA [52]. In this trial, we will avoid these flaws, and perform a more methodologically and scientifically solid study, by focusing on just the CIA, and using lesion characteristics, rather than the TASC-classification, to classify lesions.

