#### Sample size calculation

Based on the available literature [53,54], we expect a 2-year absence of binary restenosis rate of 90% in the PTFE-covered stent group, and a 2-year absence of binary restenosis rate of 72% in the uncovered stent group. Based on the log rank test for equality of survival curves, with an alpha error level of 0.05 and a beta error level of 0.2, 79 patients per group will be necessary. We anticipate a loss to follow-up of less than 10%, so we will include 87 patients per group, for a total of 174 patients. This calculation was performed using nQuery Advisor (Statistical Solutions Ltd., Farmer’s Cross, Ireland). The combined participating centers perform over 200 endovascular procedures for advanced iliac PAOD annually. With an estimated participation rate of 75%, estimated inclusion time is 2 years.

No sample size calculation was performed for the subgroups as there is no data available on freedom of binary restenosis rates for these groups, and therefore no well-founded calculation can be made.

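### The three planned subgroup pairs come only with two-arm tests, so the plan never tests whether the stent effect differs between subgroups

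*Protocol article*

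**What the plan says.** The opening of Statistical analysis covers the complete study population, "as well as subgroup analysis for patients with IC vs CLI, occlusions vs stenoses, and endovascular vs hybrid procedures". That is three factors with two levels each, so six subgroups.

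The methods follow in two subsections. Actuarial analysis gives life-table estimates with standard errors and 95% confidence intervals for restenosis and reocclusion, compared by log-rank test. Univariate analysis gives a t-test or Mann-Whitney test for continuous endpoints and a chi-squared test for categorical ones, each at P<0.05. All of these compare the two arms. The article mentions no regression model, interaction term or multiplicity rule, and it does not label the subgroup results exploratory.

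On size, the Sample size calculation section says: "No sample size calculation was performed for the subgroups as there is no data available on freedom of binary restenosis rates for these groups". Under Randomization, blinding and treatment allocation, two of the three factors (occlusion or stenosis, endovascular or hybrid) enter the minimization algorithm. Claudication versus critical limb ischemia does not.

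**The concern.** The question that a subgroup analysis can answer is whether the benefit of covered stents differs between, say, occlusions and stenoses. Two separate P values, one per subgroup, do not answer it. One may fall below 0.05 and the other above it simply because each subgroup holds only part of the patients.

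The trial was sized for about 80% power in the full sample, so each subgroup is underpowered for the same effect. The risk is a published statement that covered stents work in one kind of lesion or patient and not in another, when the data show no such difference. Readers could then restrict or extend use of the device on that basis.

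**Working it through.** **Inputs, all from Sample size calculation.**
- Covered arm: "we expect a 2-year absence of binary restenosis rate of 90% in the PTFE-covered stent group".
- Uncovered arm: "a 2-year absence of binary restenosis rate of 72% in the uncovered stent group".
- Test: "Based on the log rank test for equality of survival curves".
- Error rates and size: "with an alpha error level of 0.05 and a beta error level of 0.2, 79 patients per group will be necessary".
- Enrolment: "We anticipate a loss to follow-up of less than 10%, so we will include 87 patients per group, for a total of 174 patients".
- Sidedness is not stated. Two-sided is assumed, because it reproduces the stated 79.
- Subgroup sizes are not given, so the splits below are assumptions, from 50/50 to 90/10.

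**Step 1: reproduce the plan's figure.**
- HR = ln(0.90)/ln(0.72) = 0.321.
- Freedman events = (1.960 + 0.842)² × [(1 + 0.321)/(1 − 0.321)]² = 29.7, so 30.
- Patients per group = 30/(0.28 + 0.10) = 78.9, so 79. This matches exactly.

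**Step 2: power in one half of a pair, with the planned effect the same in both halves.**
- Expected events in the full sample: 79 × 0.38 = 30.0. Half of that is 15.0.
- Freedman: power = Φ(√15.0 × (1 − 0.321)/(1 + 0.321) − 1.96) = Φ(0.03) = 0.513.
- Schoenfeld: power = Φ(√15.0 × |ln 0.321|/2 − 1.96) = 0.596.
- Comparison of two proportions: 0.532.

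**Step 3: chance that exactly one half is significant.** The halves contain different patients, so the chance is p₁(1 − p₂) + p₂(1 − p₁). At an equal split (Freedman) it is 2 × 0.513 × 0.487 = 0.50. With 79 per group:

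| Assumed split | Power, larger / smaller (Freedman) | Exactly one significant: Freedman | Schoenfeld | Proportions |
|---|---|---|---|---|
| 50/50 | 0.513 / 0.513 | 0.500 | 0.482 | 0.498 |
| 60/40 | 0.588 / 0.429 | 0.512 | 0.499 | 0.512 |
| 70/30 | 0.655 / 0.339 | 0.550 | 0.548 | 0.554 |
| 80/20 | 0.712 / 0.242 | 0.610 | 0.627 | 0.621 |
| 90/10 | 0.762 / 0.143 | 0.687 | 0.728 | 0.706 |

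With all 87 per group followed, the lowest figure is 0.462 (equal split) and the highest 0.741 (90/10), both by Schoenfeld. The overall range is therefore 46% to 74%.

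**Step 4: check by simulation.** In 4,000 trials with 79 per group and restenosis detected at 6, 12 and 24 months, the split verdict occurred in 0.50 of trials per pair at equal splits. At least one of the three pairs split in 0.76 of trials, or 0.84 with assumed splits of 70/30, 60/40 and 80/20. Both of these treat the three factors as independent of one another.

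**Step 5: no effect at all.** The formula gives 2 × 0.05 × 0.95 = 0.095 per pair. Simulation gives about 0.09 per pair and 0.20 for at least one of three.

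**Step 6: what an interaction test would do.**
- It wrongly signals a difference in about 5% of trials per pair, whatever the common effect.
- Its power is limited. With 15 events per half, the variance of each log HR is about 4/15, so the variance of their difference is 16/30. For an interaction as large as the main effect, power = Φ(1.137/√(16/30) − 1.96) = Φ(−0.40) = 0.34.
- Events are sparse: 79 × 0.28 = 22 uncovered and 79 × 0.10 = 8 covered. Half of a pair has about 4 covered-arm events.

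**The case against.** The strongest objection is that this is detail for an analysis plan. The sentence on subgroups names three factors and gives no method. The later subsections speak of comparing the two arms and never mention subgroups, and an unseen plan may contain an interaction test. The subgroups are also few and prespecified, two of them are minimization factors, and the lack of a power calculation is admitted.

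Part of this stands. Repeating the tests within each subgroup is the natural reading, but the article does not spell it out. A separate plan could repair the matter. Still, the article does more than stay silent: it commits to the subgroups and names its tests, and none of those tests can show that an effect differs. Minimization balances the arms within a factor, but it does not compare effects across its levels.

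Some stronger readings are tempting but not supported:
- A reader might infer that split verdicts are an even bet whenever the true effect is the same in both subgroups. That holds only near the planned effect. A common effect of zero gives about 9% per pair.
- A reader might carry P<0.05 over to the subgroup log-rank tests. Among the analysis subsections, only Univariate analysis states that threshold. Actuarial analysis gives none and asks for confidence intervals, so estimation is already part of the plan.
- The Background says that grouping by lesion characteristics "allows for much more accurate analysis". A reader might take this as a promise of subgroup claims. It is an argument against TASC categories, and two of the three factors are not lesion characteristics.

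It is also fair that a better method will not make these subgroups informative, given the event counts above.

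**Conclusion.** The point holds in a limited form. As written, the plan fixes three subgroup pairs and offers only two-arm tests, so its natural outcome is separate verdicts per subgroup with no test of whether the effect differs. If the planned effect is true and uniform, a given pair shows one significant and one non-significant result about half the time at an equal split, and generally more often when the subgroups are unequal (46% to 74% over all cases tried).

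This rests on the trial's own planning rates, two-sided 0.05 tests within each subgroup, and assumed subgroup sizes. The three-pair figures also assume that the factors are independent. The primary comparison and its error rate are untouched, and nothing in the article presents the subgroups as confirmatory. It is a defect of method that should be corrected before the subgroup results are read.

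**What to change.** In Statistical analysis, state that for each of the three factors:
- the primary endpoint is analysed with a treatment-by-factor interaction, for example in a Cox model with treatment, factor and their product;
- the interaction P value is reported with an effect estimate and 95% confidence interval per subgroup, as a hazard ratio or, where events are too few, as a difference in 2-year restenosis-free proportions;
- no significance is claimed within a subgroup, and the results are labelled exploratory.

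The cost is wording only. Patients, visits and sample size do not change, and the planned software can fit the model. The drawback is low power (about 34% in the case above) and imprecise subgroup estimates with about 8 covered-arm events in total. The report should state both, so that a non-significant interaction is not read as proof of a uniform effect.
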